# STUDY POPULATION

## Population (base) Men and women with a Weber B or isolated malleolus tertius ankle fracture treated with a dorsal lower limb cast at the emergency department of both locations of the Zuyderland Medical Center, Heerlen and Sittard/Geleen, The Netherlands.

## Inclusion criteria

In order to be eligible to participate in this study, a subject must meet all of the following criteria:

- Age of 16 years and older.
- Stable ankle fracture (non-dislocated Weber B or Lauge Hansen supination-eversion stage 2-4A fracture, isolated malleolus tertius fracture).
- Conservative treatment with a dorsal lower limb cast.

## Exclusion criteria

A potential subject who meets any of the following criteria will be excluded from participation in this study:

- Age below 16 years.
- Weber A ankle fracture.
- Unstable ankle fracture.
- Fractures involving both lower extremities.
- Operative treatment of the ankle fracture.
- Posttraumatic period more than 14 days.
- Amputation of upper leg, lower leg or foot.

# TREATMENT OF SUBJECTS

## Investigational product/treatment

##
[figure not shown]
The Rebound®Air Walker is light and strong with a high degree of comfort and stability. The foot is kept in a stable plantigrade position. The advantages of a Rebound® Air Walker, above a plaster cast, are the possibilities of showering, intermediate exercise and a decrease in oedema of the ankle joint due to the built-in air compression system. Integrated pumps with coupled air cushions on the inside and outside sides ensure even compression. A valve lets the air escape when the Air Walker is removed.

Figure 3. Rebound® Air Walker

## Use of co-intervention (if applicable)

Not applicable.

## Escape medication (if applicable)

Not applicable.

# INVESTIGATIONAL PRODUCT

Not applicable.

# NON-INVESTIGATIONAL PRODUCT

Not applicable.

# METHODS

## Study parameters/endpoints

### Main study parameter/endpoint

Functional outcome scores of the ankle. This will be indicated with the Olerud/Molander Ankle Function Score (OMAS). This is a continuous variable (0-100 points).

### Secondary study parameters/endpoints

Dislocation of the fracture within 6 weeks (after placement of the Walker or circular lower limb plaster cast). This is a dichotomous variable (yes/no).

### Other study parameters

Range of motion (ROM) of the ankle and circumference of the calf (physical examination), return to work, mental health outcome scores (SF-36 questionnaire) and other complications, such as deep vein thrombosis or surgery.

## Randomisation, blinding and treatment allocation

Patients are randomized with baseline stratification (by gender, age, smoking status and diabetes) into the intervention group or the control group. For concealed allocation of the participants, a computer-generated list of random numbers will be used, which is accessible at both Zuyderland locations. Blinding of patients and researchers is not possible in this case.

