# STUDY DESIGN

A prospective randomized controlled trial at the Zuyderland Medical Center. We will include patients at both locations, Heerlen and Sittard/Geleen.

All patients with ankle fractures at the emergency department of both locations of the Zuyderland Medical Center are treated with a dorsal lower limb cast. 7 to 10 days posttraumatic, they are seen again at the traumatology department, according to protocol.

During this visit ***(= t1)****,* radiographs of the ankle joint are obtained at 3 different views (anteroposterior (AP), lateral and Mortise) and a weight-bearing radiograph (AP). When it’s a stable fracture according to the surgeon, present at that time, the patients will be approached to participate in this randomized study. If written informed consent is obtained, the patients get included.

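### Allocation is called concealed, but the only mechanism given, a random list accessible at both recruiting sites, does not secure concealment

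*Protocol*

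**What the plan says.** Protocol section 8.2 states both the aim and the means in one sentence. It announces concealed allocation and says that, for this purpose, "a computer-generated list of random numbers will be used, which is accessible at both Zuyderland locations". The same section plans stratification by four baseline factors and says of the open design: "Blinding of patients and researchers is not possible in this case".

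Section 3 describes recruitment. On place: "We will include patients at both locations, Heerlen and Sittard/Geleen". On entry at the first outpatient visit (t1): "When it’s a stable fracture according to the surgeon, present at that time, the patients will be approached to participate in this randomized study". On inclusion: "If written informed consent is obtained, the patients get included".

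Neither section says who may open the list, who holds it, or at what moment a patient's assignment becomes known.

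**The concern.** Generating a sequence at random and concealing it are separate safeguards. A computer-generated list makes the order of assignments random. It stays concealed only if the people who decide on entry cannot learn the next assignment beforehand. Section 8.2 offers the list as the means of concealment, and the one further property it states is that the recruiting sites can get at it. That property does nothing for concealment and may work against it.

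What is at stake is selection at entry. If someone who judges stability or seeks consent knew that the Walker was next, a patient with a doubtful fracture could be judged unstable, or not be approached. The arms would then differ in prognosis before treatment begins. Both the Olerud/Molander score and the comparison of dislocations could be affected, and the protocol expects dislocation to be rare.

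**Working it through.** No figure in the protocol bears on this point, so the check sets the relevant sections side by side.

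1. **Mechanism claimed (section 8.2).** Concealment is claimed, and a random list is named as the means. The protocol mentions no independent holder, central or web release, sealed envelopes or access restriction.

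2. **Where the list can be reached (sections 8.2 and 3).** The two locations with access to the list are the two locations that enrol patients. Nothing separates access to the list from the act of enrolling.

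3. **Order of events at t1 (section 3).** Radiographs are taken, the surgeon judges stability, a patient with a stable fracture is approached, consent is signed and the patient is included. The text does not say at which of these steps the list is consulted. It does not require eligibility and consent to be recorded first.

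4. **Room for judgement (sections 1, 3 and 11.4).** Section 3 rests entry on the opinion of the surgeon present. Section 1 explains that stage 4A fractures are stable only while the foot is plantigrade, so the eligible range includes cases where views may differ. Section 11.4 names dislocation as a risk of the investigational treatment. This gives a plausible reason to hold back a doubtful case if the Walker were known to be next.

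5. **Open design (section 8.2).** Treatment is not masked, so staff also see past assignments. Hiding the next one is then the main protection against selection at entry.

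6. **Whether the analysis would absorb it (sections 10 to 10.3).** The baseline variables listed are sex, age, smoking, diabetes and quality of life. Those that differ significantly between arms enter the multivariable analysis, and ANCOVA adjusts for baseline values. Fracture stage, fracture type and the surgeon's confidence in stability are not listed. Patients who never enter contribute no outcome data. The per-protocol principle concerns patients after entry and does not help.

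7. **Size.** A size would need the share of places affected and the difference in prognosis between the patients held back and those entered. The protocol gives neither. Section 4.4 does not print the means and standard deviations behind its 23 per group, so there is no stated effect to compare a bias with.

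**The case against.** The strongest reply is that section 8.2 states the intention to conceal and never says that the surgeon or recruiter can read the list. A list could be accessible at both sites through a restricted electronic release that shows one assignment at a time. This stands as far as it goes. A reader might infer that the next assignment can definitely be foreseen, but the text does not establish that.

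The protocol also has features that narrow the room for selection. Section 11.2 has all ankle-fracture patients at both emergency departments informed about the study, with a weekly check for anyone missed. Section 1 gives a radiographic definition of stability (medial clear space displacement below 3 mm and a symmetrical ankle fork). Section 3 requires three views plus a weight-bearing film. Section 10 provides for baseline adjustment. These are real safeguards, but none of them hides the next assignment, and adjustment reaches only what was measured.

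Two further inferences are tempting and not supported:

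- **That a list shared by two sites cannot deliver the planned stratification.** Section 8.2 does not describe an unstratified list, and a computer-generated list can be organised by stratum.
- **That the bias can be given a number.** Any figure would rest on invented inputs and on a target effect that the protocol does not print.

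It might also be said that this detail belongs elsewhere. How a patient is assigned at t1 is trial conduct rather than analysis, and section 8.2 does name a mechanism. The problem is the mechanism it names.

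**Conclusion.** The point holds in a limited form. Section 8.2 claims concealment, but followed as written its mechanism does not secure it. In an open trial where entry depends on a judgement made at the recruiting site, this leaves room for selection bias of unknown size, which the listed baseline variables would not fully correct. It should be changed.

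The conclusion assumes that section 8.2 is the full description of the procedure and that the sites would follow it as written. It does not assume that anyone has looked ahead in the list or would do so. If a restricted release system is already in place, the gap is one of wording and can be closed by describing that system.

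**What to change.** Replace the sentence on concealment in section 8.2 with wording such as:

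> The allocation sequence is prepared by a person not involved in enrolment and is not accessible to anyone who judges eligibility or obtains consent. Each assignment is released singly, only after eligibility and written consent have been recorded at t1, through a web module or from sequentially numbered, opaque, sealed envelopes.

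The web module is the easier choice here. Four stratification factors with at least two levels each give at least 2 × 2 × 2 × 2 = 16 strata. With the stated total of 50 patients, that is about 50 / 16 ≈ 3 patients per stratum. Envelopes kept by stratum at two sites would mean at least 2 × 16 = 32 sets, which is workable but clumsy.

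The cost is minor set-up work: preparing the module or envelopes and naming the person who holds the sequence. The change needs no extra patients or visits and leaves the treatments untouched.

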## Study procedures

| Procedures | Types |
| --- | --- |
| Radiographs | Anteroposterior(AP), lateral and Mortise view |
|  | Weight-bearing radiograph(AP) |
| Questionnaires | Olerud/Molander Ankle Function Score* |
|  | RAND Short Form 36-Item Health Survey Instrument* |
| Physical examination | Ankle dorsal flexion/ plantar flexion, with use of a goniometer. |
|  | The circumference of the calf, with use of a tapeline.***** |

********Extra procedures for this study.*

## Withdrawal of individual subjects

Subjects can leave the study at any time for any reason if they wish to do so without any consequences. The investigator can decide to withdraw a subject from the study for urgent medical reasons.

### Specific criteria for withdrawal (if applicable)

Not applicable.

## Replacement of individual subjects after withdrawal

## Not applicable.

## Follow-up of subjects withdrawn from treatment

## All data obtained until the moment of withdrawal will be taken into account in the data analysis.

## Premature termination of the study

## We don’t expect any (adverse) events that will result in premature termination of the study.

# SAFETY REPORTING

## Temporary halt for reasons of subject safety

In accordance to section 10, subsection 4, of the WMO, the sponsor will suspend the study if there is sufficient ground that continuation of the study will jeopardise subject health or safety. The sponsor will notify the accredited METC without undue delay of a temporary halt including the reason for such an action. The study will be suspended pending a further positive decision by the accredited METC. The investigator will take care that all subjects are kept informed.

## AEs, SAEs and SUSARs

### Adverse events (AEs)

Adverse events are defined as any undesirable experience occurring to a subject during the study, whether or not considered related to the experimental intervention]. All adverse events reported spontaneously by the subject or observed by the investiga­tor or his staff will be recorded.

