# OBJECTIVES

**Objective:** What are the 6-week and 12-week effects on the functional outcome scores of the ankle in early weight bearing (mobilization with Walker) compared to 6 weeks non-weight bearing and immobilization in conservatively treated stable ankle fractures (Weber B or Lauge Hansen supination-eversion stage 2-4A)?

**Secondary Objective:** What is the 6-week effect on dislocation of the fracture in early weight bearing (mobilization with Walker) compared to 6 weeks non-weight bearing and immobilization in conservatively treated stable ankle fractures (Weber B or Lauge Hansen supination-eversion stage 2-4A)?

**Other Objectives:** Other outcome measures include range of motion (ROM) of the ankle circumference of the calf, return to work, mental health outcome scores and rates of other complications.

**Hypothesis 1:** We expect earlier functional outcomes in the intervention group than in the control group.

**Hypothesis 2:** We expect the number of complications not to be higher in the intervention group than in the control group.

**Hypothesis 3:** We expect the long-term recovery function (3 months) in the intervention group not to be worse than in the control group.

**Null hypothesis 1**: The treatment in the intervention group is not as effective as the treatment in the control group, because there are worse functional outcomes in the intervention group than in the control group.

**Null hypothesis 2:** The treatment in the intervention group is not as safe as the treatment in the control group, because there are more dislocations of the fractures reported in the intervention group than in the control group.

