**Follow-up**

The patients will visit the traumatology department after 6 weeks ***(= t2)*** and 12 weeks ***(= t3)*** posttraumatic. During the visit after 6 weeks, radiographs of the ankle joint are obtained at 3 different views (anteroposterior (AP), lateral and Mortise). Furthermore, they will undergo a comprehensive examination that will include assessment of ankle dorsal flexion/ plantar flexion with use of a goniometer. The circumference of the calf will be measured with a tapeline. This will be performed by the trained research staff or by doctors trained and instructed by them.

Each visit ***(t1, t2 ánd t3)*** the patients receive 2 questionnaires with regard to return to work or sport, daily activities and limiting factors.

[figure not shown]

Figure 1. Flowchart

[figure not shown]

Figure 2. Timeline

| Variable (outcome measure) | Type | t1 | t2 | t3 | Total |
| --- | --- | --- | --- | --- | --- |
| Functional outcome score (OMAS, 0-100) | continuous | ✓ | ✓ | ✓ | 3 |
| Dislocation of the fracture (Yes/No) | binary | ✓ | ✓ | × | 2 |
| Range of motion of the ankle (degrees) | continuous | ✓ | ✓ | ✓ | 3 |
| Circumference of the calf (cm) | continuous | ✓ | ✓ | ✓ | 3 |
| Return to work (%) | continuous | ✓ | ✓ | ✓ | 3 |
| Satisfaction (SF-36, 0-100) | continuous | ✓ | ✓ | ✓ | 3 |
| Other complications | nominal | × | ✓ | ✓ | 2 |

Table 1. Measurements

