## Benefits and risks assessment, group relatedness

Benefits of the investigational treatment can be an earlier return to work or sport. Risks of the investigational treatment are myalgia and dislocation of the fracture. We expect the the latter to occur rarely, if ever.

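### Complications other than dislocation are compared between open-label arms, but no procedure asks both arms the same questions, so their count may partly reflect differences in reporting.

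*Protocol*

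**What the plan says.** Section 2 (Objectives) states Hypothesis 2 as "We expect the number of complications not to be higher in the intervention group than in the control group". Null hypothesis 2 is narrower. It calls the intervention less safe "because there are more dislocations of the fractures reported in the intervention group than in the control group", so it concerns dislocation alone.

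Section 8.1.3 adds as a study parameter "other complications, such as deep vein thrombosis or surgery". Table 1 in section 3 carries the row "Other complications | nominal", ticked at t2 and t3. Section 10.3 assigns nominal variables a chi-squared test at the 0.05 level.

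On capture, section 9.2.1 says "All adverse events reported spontaneously by the subject or observed by the" investigator or staff are to be recorded. On blinding, section 8.2 says "Blinding of patients and researchers is not possible in this case".

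Section 8.3 lists the study procedures: radiographs, two questionnaires (OMAS and RAND-36), goniometry and calf measurement. Section 3 describes the questionnaires as covering work or sport, daily activities and limiting factors.

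**The concern.** A tick in Table 1 fixes when other complications are entered. It does not say how they are found. If finding them depends on the patient raising the matter or on staff noticing, the recorded count is the product of true risk and the chance of being recorded. In an open trial that chance can differ between arms.

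The protocol gives reasons why it might. Section 5.1 lists among the Walker's advantages over plaster "the possibilities of showering, intermediate exercise", so Walker patients can see and handle the leg, while control patients wear a circular cast until 6 weeks. Section 11.4 says "Risks of the investigational treatment are myalgia and dislocation of the fracture". Myalgia is thus named for one arm only, and no listed procedure measures it.

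What is at stake is the non-dislocation part of Hypothesis 2. A difference in recording could produce an apparent excess or hide a real one.

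**Working it through.** **Where each Table 1 outcome comes from (sections 3 and 8.3)**

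| Outcome | Stated source |
|---|---|
| OMAS | questionnaire |
| Dislocation | radiographs; CT on suspicion (section 10.2) |
| Range of motion | goniometer |
| Calf circumference | tape |
| Return to work | questionnaires |
| SF-36 | questionnaire |
| Other complications | none stated |

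Other complications is the one row with no instrument, question or definition. The only text on how such events are recorded is section 9.2.1.

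**What unequal capture would do**

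The protocol gives no complication rate and no capture rate, so it has no figure to reproduce. Every rate below is an assumption; only the 23 per group comes from the protocol (section 4.4).

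Observed risk ratio = true risk ratio × (capture in Walker arm ÷ capture in cast arm).

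| True risk ratio | Capture, Walker v cast | Observed risk ratio |
|---|---|---|
| 1.0 | 90% v 70% | 0.90/0.70 = 1.29 |
| 1.0 | 70% v 90% | 0.70/0.90 = 0.78 |
| 1.0 | 80% v 50% | 0.80/0.50 = 1.60 |
| 1.0 | 50% v 80% | 0.50/0.80 = 0.625 |
| 1.5 | 50% v 80% | 1.5 × 0.50/0.80 = 0.94 |

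These ratios do not depend on the underlying risk.

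**Expected counts**

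With 23 per arm, a 20% true risk in both arms and 80% v 50% capture:

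- Walker: 23 × 0.20 × 0.80 = 3.7 recorded events
- Cast: 23 × 0.20 × 0.50 = 2.3 recorded events

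**Would this change the test?**

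Rounded to 4/23 v 2/23, the uncorrected chi-squared statistic is 46 × (4×21 − 2×19)² ÷ (6 × 40 × 23 × 23) = 46 × 46² ÷ 126,960 = 0.77, so p is about 0.38. One event fewer in the higher arm and one more in the lower turns 4 v 2 into 3 v 3. One or two reports can thus remove or reverse the observed ordering, but they do not move this test near 0.05.

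**The case against.** The strongest reply is that complications are not left to chance. Table 1 makes them a scheduled measurement in both arms at two visits. Section 9.2.1 sits under safety reporting and does not say that it replaces that schedule. Both devices come off at 6 weeks, and all patients are then examined. The two named examples, thrombosis and surgery, are fairly hard events. The wording of visit questions often sits in a case report form, which is not at hand. The asymmetry is also not all one way: the introduction names thrombosis and pulmonary embolism as risks of plaster immobilisation.

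Most of this stands as a limit on the point. Three stronger readings are tempting, and the documents do not support them:

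- A reader might infer that every complication is captured only if volunteered or noticed. Dislocation is sought by three-view radiographs in all patients at 6 weeks, and other complications do have scheduled entry points.
- A reader might infer that the whole safety conclusion is compromised. Null hypothesis 2 and the secondary endpoint are dislocation, which does not depend on section 9.2.1.
- A reader might infer that the count is in fact biased, or that one or two reports would change the test result. Differential reporting is a risk, not something the protocol shows, and the p of about 0.38 above does not bear out the second claim.

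What the reply does not meet is that the protocol states a passive rule in its own text and names no common question for the two arms. This is a data-collection matter: an analysis plan cannot recover events that nobody asked about.

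**Conclusion.** The point holds for complications other than dislocation, and most for subjective events such as myalgia. Their between-arm count may partly reflect differences in reporting. Under the assumed capture rates, equal true risks appear as risk ratios between 0.625 and 1.60, and a true 1.5 can appear as 0.94. Those rates are illustrations and are least plausible for thrombosis and surgery. Neither the size nor the direction of any real difference can be derived from the documents. The change should be made before data collection, though it concerns an outcome ranked below the primary and secondary endpoints. If a case report form already puts one identical list to both arms, the protocol need only say so.

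**What to change.** In sections 8.3 and 9.2.1, keep spontaneous and observed reporting. Add that at t2 and t3 every patient in both arms is asked the same short closed list of complications, in the same words, with a date for each event. The list should at least cover the events the protocol itself names (muscle pain, thrombosis, surgery) and could add skin or pressure problems and falls.

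Use these answers for the between-arm comparison of other complications, and list purely spontaneous events separately. Leave dislocation on its scheduled radiographs, as the secondary endpoint and the test of null hypothesis 2; the list must not displace it.

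The cost is a short form at two visits that already take place, and more minor events recorded in both arms. Asking both arms alike reduces reporting bias for subjective symptoms but cannot remove it while patients know their treatment.
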